## Abstract

**Background:**

Total hip arthroplasty (THA) is a common and effective surgical method for advanced hip arthritis. Rehabilitation exercises are important to improve joint function after THA and are usually conducted in a home-based program. Poor patient adherence limits improvements in pain and function, affecting quality of life. The increasing use of THA in the aging Chinese population underscores the need to develop strategies that maximize functional outcomes. The purpose of this pilot study is to develop and assess the feasibility of a self-efficacy-enhancing intervention (SEEI) to improve exercise adherence in patients undergoing THA.

**Methods:**

This single-blinded, parallel, randomized control trial will recruit 150 patients after THA and randomly assign them to an intervention or control group using computer-generated block randomization. The control group will receive usual care using evidence-based guidelines. The intervention group will receive the 6-month SEEI comprising personalized exercise guidance and self-efficacy education delivered using one face-to-face education session and four telephone consultations, supplemented by written materials. Participants are encouraged to build confidence in their own abilities, set rehabilitation goals, and self-monitor their physical exercise.

**Results:**

Assessments will be conducted at baseline and 1, 3, and 6 months postsurgery. The outcome indicators are exercise adherence, physical function, anxiety and depression, self-efficacy of rehabilitation, joint function, and quality of life.

**Conclusions:**

This study will test a theory-based intervention program to improve self-efficacy in rehabilitation, which may significantly impact out-of-hospital rehabilitation. The results will provide evidence to inform the postoperative recovery of patients undergoing THA or similar procedures.

**Trial registration:**

Chinese Clinical Trials Registry, ChiCTR2000029422, registered on 31 January 2020

## Background

Total hip arthroplasty (THA) is a major surgical procedure performed worldwide [1]. Approximately 400,000 THAs are performed annually in China [2], and this is growing rapidly due to the high level of patient needs and the challenges of an aging population [3, 4]. THA is a cost-effective intervention that reduces or even eliminates pain [5]. Despite these encouraging facts, differences remain in patient self-reported functional improvement after THA [6, 7]. Some studies have reported significant positive correlations between the surgical effects in patients after hip/knee arthroplasty and exercise adherence [8–11]. Exercise adherence is indeed a fundamental determinant to the success of hip arthroplasty, as plenty of new technologies and integrated pathways aim to enhance [12]. Home exercise adherence is usually high in the early stage but gradually decreases over time [13, 14]. As poor adherence to home exercise is common and affects therapeutic effectiveness and healthcare costs [15], there is an urgent need for economic, achievable, and effective interventions to improve home exercise adherence [16].

Self-efficacy is an important part of promoting healthy behavior and a significant determinant influencing the initiation and maintenance of positive health behaviors [17, 18]. The concept of self-efficacy was first proposed in 1977 [19]. According to self-efficacy theory, if individuals believe that they can achieve results, then they become more active and in control of their lives. A high sense of individual self-efficacy can lead to positive health behaviors [19, 20]. A higher sense of self-efficacy indicates that individuals will exhibit good exercise adherence, while a lower sense of self-efficacy is regarded as an obstacle to ensuring effective rehabilitation [21].

A number of studies have shown that enhancing self-efficacy is helpful to patient self-management and promotes health-related behaviors and good outcomes. Related interventions have been successfully applied in people with coronary heart disease [22], diabetes [23], hypertension [24], stroke [25], arthritis [26], and joint replacement rehabilitation [27, 28]. Therefore, patients should believe in their ability to perform specific physical activities to improve their rehabiliation after THA. Previous investigations have shown moderate self-efficacy of Chinese patients after hip and knee arthroplasty [29, 30]. Nevertheless, studies in this field are scarce, the majority used small sample sizes, and self-efficacy has not been considered in rehabilitation program development, leading to substantial extension of rehabilitation times and unsatisfactory outcomes.

The theory of self-efficacy provides a good basis for nursing interventions for patients after THA. This study is inspired by the self-efficacy theory of Bandura, which proposes that enhancement of self-efficacy is beneficial for patient rehabilitation and for achieving optimal outcomes. To investigate this further, we developed a 6-month self-efficacy-enhancing intervention (SEEI), to support adherence to prescribed home-based exercise for patients following THA. The SEEI was developed in rigorous accordance with Bandura’s self-efficacy theory and is a complex intervention. That theory is here applied to rehabilitation after THA.

Our primary hypothesis is that adherence to the prescribed home exercise program in the 6 months after THA will be higher in the group receiving the SEEI compared with the group receiving usual care. Our second hypothesis is that the SEEI group will exhibit greater improvements in other outcomes (e.g., pain, function, health-related quality of life [QOL], anxiety and depression, and another measure of exercise adherence) than the control group.

## Methods

### Study design

This prospective randomized controlled trial is to test the effect of a nurse-led SEEI, inspired by the theory of self-efficacy, and aimed to increase patient compliance following THA. All participants are randomly assigned to the SEEI group or usual care (control) group. This study will examine the effect of the intervention on patient exercise compliance after THA and evaluate the contribution of the intervention to the improvement of joint function. We hypothesize that participants in the experimental SEEI group will show significantly better exercise self-efficacy, a greater increase in exercise compliance, superior hip function, lower levels of anxiety and depression, and increased QOL. Data will be assessed at baseline and 1, 3, and 6 months after surgery. The study has been approved by the Ethics Committee of our institution and will be registered, constructed, and presented following the recommendations of the CONSORT statement [31] and SPIRIT guidelines [32] (see Fig. 1).

**Fig. 1 Fig1:**
[figure not shown]
Flow diagram of the trial procedures

### Setting and population

The study setting is the Joint Surgery Unit of the Orthopedics Department at a hospital.

Patients on the surgical waiting list for THA will be invited to participate in the study after preoperative assessment. Men and women aged 18 years or older and scheduled for primary, single-side THA surgery at the Joint Surgery Unit are eligible for participation. Trial inclusion criteria are the following: participants must be able to read and understand Chinese, be willing to participate in a 6-month exercise intervention, and provide informed consent. Participants are ineligible if they meet one or more of the following exclusion criteria: (i) an unstable medical condition due to fracture, malignancy, infection, or THA failure; (ii) inability to provide informed consent due to mental disorder, dementia, or cognitive impairment that prevent completion of self-report surveys; (iii) co-existing conditions that would negate functional improvement with surgery and exercise (e.g., severe Parkinson disease, or hemiparesis); (iv) simultaneous bilateral THA; (v) surgery for neoplastic disease or imminently scheduled surgery and unavailable to complete the study procedures (e.g., bone tumor surgical operation); and (vi) planning another THA or total knee replacement within 6 months.

### Development of the SEEI program

#### Preparation phase

After reviewing international guidelines on the development of exercise interventions for adults undergoing hip surgery, the preparation of the SEEI program followed a three-stage process:
i)Setting up a nurse-led intervention team, mainly composed of orthopedic nursing clinical specialists, orthopedic surgeons, orthopedic physicians, senior orthopedic nurses, and research assistants, to control the overall research direction, formulate and evaluate intervention programs, and control the quality of research. A draft intervention was produced after a series of interviews with patients undergoing THA by experienced healthcare professionals; the specific content and protocol were subsequently validated by a panel of orthopedic experts.ii)Formulating the “Handbook for Rehabilitation after discharge following THA” including two main aspects: post-discharge guidance, including general information about home reorganization, functional exercise, matters or follow-up needing attention, and daily life guidance during each rehabilitation period after THA; and a functional exercise diary in the rehabilitation manual that is convenient for patients to record their exercises and any problems. The functional exercise and daily life guidance sections contain illustrations and detailed written explanations. Contact information for the department, orthopedic specialist, and orthopedic nurse is at the back of the guide. The handbook will be available for patients in both groups.iii)Registering a WeChat account for research and filming a functional exercise video. A WeChat account has been created specifically for the experimental group and is managed by a research assistant, as a convenient means to establish multiple contacts with patients and reduce follow-up loss. WeChat is used to promote exercise videos provided for patients and their families to learn about the various stages of joint replacement rehabilitation. WeChat will also be used to collect video data, including exercise and walking, during the rehabilitation process.

#### Intervention theoretical framework

The intervention is based on Bandura’s self-efficacy theory [33], combined with social cognitive theory (SCT) [34]. Social cognitive theory regards self-efficacy as an internal factor, influencing learner autonomy greatly by affecting learners’ goal setting, self-monitoring, self-evaluation, and strategy use [34]. Consistent with SCT, interventions target self-management knowledge, attitudes (self-efficacy), and behavioral abilities through a variety of printed materials and activities. The intervention program is also conducted according to Bandura’s self-efficacy theory [35], which includes four main aspects: individual past experience, witnessing the experiences of other individuals, verbal motivation from others, and physical and emotional support for patients, specific to the particular behavior [20]. The four strategies recommended by Bandura [36] have been incorporated into each component of the intervention. Individual past experience includes emphasizing the importance of functional exercise, helping participants to set achievable goals, encouraging them to observe and record their exercise behavior, and accumulating self-management experience according to their subjective physical experience. Vicarious experience includes sharing successful examples of patients who have experienced similar symptoms and recovered using self-management skills, to help participants build confidence, and encourage them to adhere to the functional exercise program. Verbal persuasion includes describing the benefits of exercise adherence to joint function, encouraging and acknowledging the participant’s ability to deal with symptoms, and helping those who encounter difficulties in finding specific causes and the following most suitable solutions. Physical and emotional support includes the explanation of possible symptoms during postoperative rehabilitation and the discussion of treatment strategies. Patients are supported in these four strategies during training sessions. Table 1 outlines examples of the four strategies [19].

**Table 1 Tab1:** SEEI components, strategies, and techniques

Components	Strategies	Specific techniques
Individual past experience	• Setting achievable goals • Providing information on the benefits of functional exercise • Providing positive feedback	• Consulting with patients to develop functional exercise goals at different stages; making plans on when, where, and how to conduct regular physical activities • Providing information on the risk factors of a sedentary lifestyle and the advantages of functional exercise • Identifying postoperative rehabilitation challenges through discussion • Providing positive feedback on patient accomplishments
Vicarious experience	Sharing cases of successful rehabilitation	• Sharing previous success stories to build confidence • Introducing the successful experiences of others to encourage patients to complete physical activities in the following months
Verbal persuasion	Verbal encouragement, explanation, and persuasion	• Describing the benefits of physical activities • Asserting that patients have the ability to self-manage • Providing positive feedback on the patient’s efforts and giving verbal encouragement • Reinforcing the past and present successes or accomplishments of patients
Supporting patients physically and emotionally	• Developing strategies to cope with barriers • Help to seek social support	• Assessing patient expression of anxiety and depression • Identifying individual barriers to and resources for physical activity • Providing strategies for dealing with barriers and coping in the future (postsurgery; significance of social support)

#### Intervention structure and content

Challenges to successful post-THA functional achievement were identified, and strategies to address them were developed and integrated to design the intervention. Telephone interview was selected as the primary basis for the intervention because it is a low-cost, wide-coverage mechanism that can provide support intervention after THA for patients with limited mobility and transport difficulties [37]. Although this format has not been thoroughly investigated in patients with THA, it has been well-studied for patients with other conditions and used alone or in combination with face-to-face educational sessions and print materials [38, 39]. The initial intervention was further refined following a pilot pretest involving five patients.

The final intervention protocol includes a total of five sessions: 1 h of face-to-face education before discharge, and four additional sessions post-discharge between 1 and 6 months after surgery. Except for the hospital visit, all visits are telephone-based. The first call is approximately 40 min, with follow-up contacts ranging from 20 to 30 min. The intervention aims to enhance exercise adherence through the implementation of self-efficacy-enhancing strategies.

The initial face-to-face intervention is conducted in the hospital office before patients are discharged from the hospital after THA surgery. The focus of the initial session is to assess the functional exercise status and psychological condition of each individual, including the level of pain, the occurrence of complications, and knowledge of functional exercise. The nurse provides participants with the Rehabilitation Handbook after THA and instructs them to read it. The manual is used to supplement the face-to-face educational session. Participants are encouraged to refer to the manual at home for information. The nurses also provide video recordings of functional exercise after THA and teach patients the functional exercise movements and matters needing attention in daily life after surgery, as well as persuading and encouraging participants to set rehabilitation goals to be achieved 1 month post-THA, and mobilizing the encouragement and support of the participant’s family members.

During the 6-month follow-up period, four subsequent health-coaching sessions are conducted via telephone or the WeChat app. These sessions are designed to enhance participant compliance with functional exercises and are guided by a protocol. Participants in each follow-up are required to self-report the number of home exercises they have completed in the previous week, their level of pain, and their mental state. Nurses encourage and provide reinforcement of the participant’s efforts and success and empower them through support. Participants with a low adherence (<3 exercise sessions/week) are then asked to select a barrier from a scheduled list (forgot, too tired, injured, fear of movement, exercise inconvenience, lack of time, life stress) to explain why they were unable to complete the exercise as required. The nurse then provides a suggestion tailored to help overcome that barrier. According to the needs of each patient, the duration of each phone call ranges from 20 to 30 min.

Four senior orthopedic nurses with bachelor degrees or above and at least 10 years of orthopedic nursing experience have been selected in the target hospital. All nurses have orthopaedic specialist nurse certificates and are very familiar with the rehabilitation needs and physical and psychological problems of patients after THA. They are required to establish close relationships with the patients. Simultaneously, two research assistants are assigned to conduct the interventions with the patients, primarily through collection of questionnaire data, and assist with relevant intervention content. The two research assistants are very familiar with the care of patients undergoing joint replacement. Two days of training are provided for the nurses before intervention implementation, primarily including communication skills, consistency of the intervention program, strategies to encourage physiological and psychological changes, detailed descriptions of problems that occur in the rehabilitation process after THA, dos and don’ts for the telephone follow-up, and matters included in the intervention follow-up record form. All staff also receive training on the study protocol and the procedures for collecting informed consent and data assessment. The principal investigator will monitor the conduct of the intervention through observation sampling sessions.

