### Assessment of outcomes

All assessment sessions (baseline [time 1], 1 month [time 2], 3 months [time 3], and 6 months [time 4] postsurgery) include measurement of the primary and secondary outcomes. A series of questionnaires related to health outcomes of the SEEI is implemented. During the baseline assessment, additional demographic information including health, medical history, and general health status is collected.

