##### Hip function

Hip function is monitored using the Harris Hip Score (HHS) for hip arthroplasty, a multidimensional disease-specific observational assessment of functioning, containing eight items representing pain, walking function, activities of daily living, and range of motion of the hip joint [50]. The HHS is widely used by physicians to assess physical function and pain relief in patients with hip disease [51]. The maximum score for the HHS is 100 points, with maximum possible scores for its components as follows: pain (44 points), function (47 points), range of motion (5 points), and deformity (4 points) [52]. A higher HHS score indicates better function.

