### Randomization and blinding

After completing all baseline data collection measures, participants are randomly divided into the intervention and control groups using computer-generated random numbers. Participants are assigned a series of continuous integers in the order of admission. To hide randomization, the independent researcher has prepared consecutively numbered, sealed, opaque envelopes, which are kept in a locked location. To avoid affecting exercise adherence behavior, participants are not informed of the two separate studies, re-randomization into this trial, or the exact details of the intervention. This process ensures adequate concealment, limiting the possibility of selection deviation. The statistician will be blinded to group allocation, which will be revealed upon completion of the statistical analyses.

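### Staff with a role in delivering the intervention appear to collect the outcome questionnaires, and only the statistician is named as blinded to allocation

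*Protocol article*

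**What the plan says.** All places are in the protocol article.

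- **Label.** The abstract's Methods paragraph opens: "This single-blinded, parallel, randomized control trial will recruit 150 patients after THA". It does not say who the blinded party is.
- **Who is blinded.** Under Randomization and blinding: "The statistician will be blinded to group allocation, which will be revealed upon completion of the statistical analyses". No other party is described as blinded to allocation.
- **What participants are told.** The same section says that "participants are not informed of the two separate studies, re-randomization into this trial, or the exact details of the intervention". The stated aim is to leave their exercise behaviour undisturbed.
- **The research assistants.** Under Intervention structure and content: "two research assistants are assigned to conduct the interventions with the patients, primarily through collection of questionnaire data, and assist with relevant intervention content".
- **The WeChat account.** Under Preparation phase: "A WeChat account has been created specifically for the experimental group and is managed by a research assistant".
- **Outcome measurement.** Under Assessment of outcomes: "A series of questionnaires related to health outcomes of the SEEI is implemented". This covers baseline and months 1, 3 and 6. No collector is named there.
- **Primary outcomes.** The self-efficacy scale asks patients how confident they are. The compliance scale asks how often they follow each exercise behaviour.
- **Hip score.** Under Hip function, the Harris Hip Score is "a multidimensional disease-specific observational assessment of functioning". No rater is named.

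**The concern.** One sentence gives the two assistants both jobs: a part in the intervention and the collection of questionnaires. Anyone who helps with SEEI content, or runs a messaging account that exists for one arm only, knows which patients are in that arm. If the same people collect the follow-up questionnaires, the collector is not blinded, and blinding the statistician does not change that.

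The outcomes are of the kind that a collector can influence. Both primary scales are patients' ratings of their own confidence and compliance, which are what the intervention sets out to raise. How a question is put, prompted or clarified can move such an answer. The likely direction favours SEEI. Neither a larger sample nor the repeated-measures model in Data analysis would remove a shift of this kind, because it enters with the data.

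**Working it through.** **Step 1: does the text put both roles on the same people?**

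| Question | Source section | Answer |
|---|---|---|
| Do the assistants have an intervention role? | Intervention structure and content | Yes, stated |
| Does an assistant have contact with one arm only? | Preparation phase | Yes for one assistant, through the WeChat account |
| Do the assistants collect questionnaires? | Intervention structure and content | Yes, stated, but the scales are not named |
| Are the outcomes questionnaires? | Assessment of outcomes, and the scale descriptions | Yes, apart from the observer-rated hip score |
| Is another collector named? | Whole article | No. Staff as a whole are trained in assessment procedures, but none is set apart as independent |
| Is any collector or rater blinded? | Randomization and blinding | None is mentioned |

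The first three answers are explicit. That the questionnaires in question are the outcome scales follows from the next two. It is a strong inference, not a statement.

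**Step 2: how large could the effect be?** The article gives no figure for reporting or assessment bias, so this step only illustrates how sensitive a trial of this size is.

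Inputs:
- 64 patients per group (Sample size calculation). As a check on the plan's total, 128/(1 − 0.15) = 150.6, against 150 stated; the figures agree to within a patient. The 64 itself is taken as given, because the article states no effect size, SD or power.
- Alpha 0.05 (Data analysis). Sidedness is not stated; two-sided is assumed.
- No true effect, and a shift of *b* SD in one arm only. The values of *b* are assumptions.

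Formulae for a simple two-group comparison of means in SD units:
- SE = √(2/64) = 0.177
- P(significant) = 1 − Φ(1.96 − b/SE) + Φ(−1.96 − b/SE)

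| Assumed shift b (SD) | b/SE | P(significant) |
|---|---|---|
| 0 | 0 | 5% |
| 0.1 | 0.57 | 0.087, about 9% |
| 0.2 | 1.13 | 0.205, about 20% |
| 0.3 | 1.70 | 0.396, about 40% |

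The planned analysis is a repeated-measures multivariate analysis of variance, so these figures stand in for it and do not predict its error rate. They also do not separate the part of a shift due to the collector from the part due to patients who know they had extra support.

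**The case against.** There is a fair case on the other side, and much of it stands.

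*The assistants are not the coaches.* A reader might infer that SEEI patients report their adherence to the people who coached them. The article does not support that. Teaching, goal setting, encouragement and advice on barriers are given to the nurses, who are also the ones asked to build rapport. The assistants' work is mainly questionnaires, with some help on content, and the WeChat account is run by one of them. What remains is knowledge of allocation and some intervention contact, which is weaker than a coaching relationship.

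*The questionnaires are not named.* Each follow-up contact also gathers self-reports of exercise, pain and mood, and there is a follow-up record form, so the assistants' questionnaire work could mean that. This is possible, but then the article assigns nobody to the outcome scales.

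*The hip score.* A reader might infer that the assistants rate it. Nothing says so. The rater is unstated, so bias there is a possibility and no more.

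*Participants are partly masked.* Details are withheld from them, so the single-blind label may be meant for participants rather than the statistician. That is a real measure, but it is not blinding to allocation. Patients who receive an hour of education and four coaching contacts can tell that they are being supported. It also does nothing to blind the collector.

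*The patient is the assessor on a self-rated scale.* This is correct. A blinded collector limits prompting and expectation; it does not stop patients giving the answer they think is wanted.

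**Conclusion.** The point holds in a limited form. As written, the plan gives the same two assistants a part in delivering SEEI and in collecting questionnaires, names no other collector, and names only the statistician as blinded to allocation. By strong inference, outcome data are collected by staff who know allocation. That exposes the two self-rated primary outcomes to collector influence in favour of SEEI. It leaves open whether the hip score is rated by someone who knows the arm. It also leaves the single-blind label without a clear referent.

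The size is unknown. The 9%, 20% and 40% figures are arithmetically correct for shifts of 0.1, 0.2 and 0.3 SD, 64 per arm, two-sided 5% and a simple comparison. The shifts are assumed, and it would be wrong to read the figures as this trial's false-positive rate.

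**What to change.** 1. **Divide the assistants' duties.** One supports the SEEI sessions and the WeChat account. The other has no intervention role, is not told allocation, and collects all questionnaires at 1, 3 and 6 months in both arms. Baseline needs no such protection, because it is completed before randomization.
2. **Self-completion.** Patients fill in both primary scales themselves, outside any coaching contact.
3. **Hip score.** Have it rated by existing staff with no part in the intervention who are not told allocation, and say who they are.
4. **Text.** In Randomization and blinding, state for participants, intervention staff, questionnaire collector, hip-score rater and statistician whether each is blinded. Reconcile this with the partial masking of participants and with the label in the abstract.
5. **Limitations.** List participants' own reporting bias on the self-rated outcomes, which these steps do not remove.

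Cost: no new staff, but less cover for absence and a heavier load on one assistant, at most 150 × 3 = 450 questionnaire sessions after randomization. The Discussion calls the trial ongoing. Data already collected cannot be repaired, and an assistant who has already worked with SEEI patients may know some allocations. The report should therefore say from which date the separation applied.
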